### Randomization and allocation concealment

2.5

Subjects will be assigned a trial number (1–372) in the order in which they are registered. We will use a block randomization method to randomly assign subjects to the intervention and control groups in a 1:1 ratio with variable block lengths (2, 4, 6, 8). The randomization scheme will be the responsibility of a dedicated person ([name]) from the clinical trial center who will not be involved in other parts of the trial. The randomization scheme will be placed in a sealed, opaque envelope. The quality controller ([name]) will open the envelopes in the order of their enrollment before the start of the trial, and subjects will be grouped according to the allocation scheme in the envelope. The quality controller will not participate in other parts of the trial.

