### Sample size calculation

2.3

The sample size for this trial is based on the incidence of POD. A previous meta-analysis reported a 17% incidence of POD in patients who underwent a total joint arthroplasty (Scott et al., 2015). When considering the potential effect of the study intervention, we used the absolute risk reduction of 10% (corresponding to a number needed to treat of 10 patients) recommended by previous studies (Avidan et al., 2017). We therefore assumed that the incidence of POD in the intervention group would be 7%. We used Power Analysis and Sample Size version 15.0 (Stata Corp. LP, College Station, TX, United States) to calculate a sample size of 166 per group. Considering a 10% lost to follow-up rate, at least 186 subjects in each group and 372 subjects should be included.

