### Anesthesia and perioperative analgesia

2.8

Subjects received oral celecoxib 200 mg (Pfizer pharmaceutical co., Ltd., Dalian, Liaoning, China) once daily prior to surgery. Subjects will be transferred to the anesthesia induction room on the day of surgery. Peripheral venous access will be obtained and 3-lead ECG, noninvasive blood pressure, and oxygen saturation monitoring will be established. Depending on the type of procedure, each subject will undergo either an ultrasound-guided adductor canal block or an iliac fascial block before anesthesia induction. Twenty minutes after the block, the subject will be transported to the operating room for intraspinal anesthesia. As this is a pragmatic clinical trial, the use of anesthetic drugs and techniques (epidural vs. subarachnoid block) is at the discretion of the anesthesia team that is assigned to each subject. The anesthesiologist can choose the appropriate medication regimen according to their clinical practice. However, the anesthesia team needs to use the study drug according to the guidance of the drug administrator. The team will also be asked to avoid the use of benzodiazepines, dexmedetomidine, S-ketamine, and other NMDA receptor antagonists. During the surgery, the patient’s body temperature will be continuously monitored with a body temperature monitor to maintain their body temperature at 36°C–37°C. Subjects with hypothermia will be treated with a warm air blower. Infusion and transfusion will be performed according to routine procedures, and blood pressure will be maintained within 20% of baseline. Twenty minutes before the end of surgery, the anesthesiologist will administer ondansetron 4 mg (Qilu Pharmaceutical Co., Ltd., Jinan, Shandong, China) to prevent nausea and vomiting. The PCIA device will be activated in the post-anesthesia care unit (PACU). When the subject’s Number Rating Score (NRS) rises above 4 points, they will receive intravenous fentanyl 50 μg (Jiangsu Enhua Pharmaceutical Co., Ltd., Xuzhou, Jiangsu, China) as rescue analgesia. Subjects will be transferred to the surgical ward when they meet the transfer criteria. Subjects will receive flurbiprofen axetil 50 mg (Beijing Taide Pharmaceutical Co., Ltd., Beijing, China) twice daily as basic analgesic therapy. When the subject’s NRS rises ≥4, they will receive an intravenous injection of 50 mg pethidine (Qinghai Pharmaceutical Factory Co., Ltd., Xining, Qinghai, China), which can be repeated every 4–6 h, with a maximum dose of 300 mg per day. Rescue analgesia is adequate when the subject’s NRS is <4 points. In the case of moderate to severe postoperative nausea or vomiting, ondansetron 0.1 mg/kg will be administered intravenously.

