#### Intraoperative data

2.14.2

Type of surgery (TKA/THA), surgery time (min), anesthesia time (defined as time elapsed from anesthesia induction to the end of surgery, min).Blood loss (mL), infusion volume (defined as the total volume of crystalloid and colloid, mL), and transfusion volume (mL).Steroid dosing (mg).

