### Statistical methods

2.16

To analyze the primary study outcome, we will use the ITT analysis set. The ITT analysis set is defined as all subjects who undergo randomization regardless of their intervention. Data processing and analysis will be performed using R version 4.3.0 and the Storm Statistical Platform.^1^ Continuous variables will be tested for normality using Shapiro–Wilk, with normal data expressed as mean ± SD, non-normal data as median and interquartile range, and categorical data as number of cases (n) and percentage (%). For demographic data, baseline characteristics, and intraoperative data, quantitative data between the two groups will be compared using a two-independent sample t-test or Mann–Whitney U test, and qualitative data will be compared using the chi-square test, continuous corrected chi-square test, or Fisher’s exact test. The primary outcome is a dichotomous measure, and the odds ratio (OR) and 95% confidence interval (CI) of the incidence of POD between the intervention and control groups will be calculated using a logistic regression model. This is a pragmatic study, and potential confounding variables may bias the degree of association between interventions and primary outcomes. The logistic regression model will therefore include demographics and baseline characteristics as covariates. We plan to build four different models. Model 1 will only include grouping factors and not control for confounding factors. The net OR and 95% CIs will be calculated. Model 2 will adjust for sex, age, ASA classification, comorbidities, and education level. Model 3 will adjust for electrolyte abnormalities, hypoproteinemia, and anemia based on Model 2. Model 4 will adjust for smoking, alcohol use, history of falls, vision or hearing abnormalities, preoperative dementia, depression, functional status, frailty, sleep disorders, and aCCI based on Model 3. Adjusted OR and 95% CIs will be calculated from Models 2, 3, and 4. We will perform a sensitivity analysis on the primary outcome to compare the effects of different analysis sets (ITT and PP) and statistical methods (modified Poisson regression and logistic regression) on the robustness of the primary outcome. The PP analysis set excludes subjects who did not meet our eligibility criteria or had incomplete adherence to the trial medication. Subgroup analyses will be performed for age, gender, dementia, depression, frailty, sleep disorders, vision or hearing abnormalities, and functional status, and interactions will be investigated.

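### Surgery type (hip or knee) is recorded and in effect known at allocation, but no adjusted model includes it: a small, nearly free loss of precision, not a bias

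*Protocol article*

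**What the plan says.** All references are to the protocol article; the statistical analysis plan is not shown.

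- **Allocation (2.5).** "We will use a block randomization method", 1:1, with block lengths of 2, 4, 6 and 8, over a single run of trial numbers from 1 to 372. No stratification factor is named.
- **Eligibility and timing (2.2.1 and Table 2).** Planned hip or knee arthroplasty is an inclusion criterion. Screening and randomization are both placed at Visit 1, the day of admission.
- **Co-intervention (2.8).** "Depending on the type of procedure, each subject will undergo either an ultrasound-guided adductor canal block or an iliac fascial block".
- **Data collection (2.14.2).** The intraoperative list opens with "Type of surgery (TKA/THA), surgery time (min". Surgery type is not in the baseline lists of 2.7 and 2.14.1.
- **Primary models (2.16).** Model 1 has treatment only. "Model 2 will adjust for sex, age, ASA classification, comorbidities, and education level". Model 3 adds three laboratory items to Model 2, and Model 4 adds ten further items to Model 3. Surgery type is in none of them, nor among the subgroup factors.
- **Secondary models (2.16).** Timed Up and Go, active range of motion of whichever joint was operated on, and Barthel index go to ANCOVA with the baseline measurement as covariate. NRS scores and opioid consumption go to GEE. No surgery-type term is named for either.

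**The concern.** Section 2.16 justifies its long covariate lists by the risk that baseline factors distort the treatment comparison, and the Discussion calls it crucial to identify such factors. The lists are written out model by model, so this is not a detail the article defers. They nevertheless omit the variable that defines the two pooled populations and determines their regional block.

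Two things are at stake. First, a chance imbalance in the hip/knee mix would not be corrected in any planned odds ratio. Section 2.16 does compare intraoperative data between arms, so an imbalance would be seen, but a covariate added at that stage would be post hoc. Second, some outcomes put measurements from two different joints, or from patients with two different blocks, into one model. Any difference between operations that the baseline value does not explain then stays in the residual.

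**Working it through.** **1. The plan's own sample size.** Inputs from 2.3: "A previous meta-analysis reported a 17% incidence of POD in patients who underwent a total joint arthroplasty"; "incidence of POD in the intervention group would be 7" percent; "calculate a sample size of 166 per group"; "Considering a 10% lost to follow-up rate". From 2.16: two-sided tests at 0.05. Power is not stated; 80% is assumed because it reproduces the figure.

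n = [1.96·√(2·0.12·0.88) + 0.8416·√(0.17·0.83 + 0.07·0.93)]² / 0.10² = (0.9007 + 0.3822)² / 0.01 ≈ 164.6, so 165 against 166 stated. After loss: 166 / 0.90 = 184.4, so 185 against 186 stated. Both reproduce to within one patient. Surgery type plays no part in this calculation, and adjusting for it leaves the planned number unchanged.

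**2. Is the joint known at allocation?** No sentence says so. It follows from 2.2.1 (the planned operation is an eligibility condition) read with Table 2 (screening and randomization at the same visit). The inference is sound.

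**3. Chance imbalance.** The documents do not give the hip:knee mix, so the hip share q is assumed. With 186 per arm, SD of the between-arm difference = √[2q(1−q)/186].

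| Assumed q | SD | P(difference > 10 points) |
|---|---|---|
| 0.30 | 4.8 points | 3.5% |
| 0.50 | 5.2 points | 5.4% |

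At q = 0.50, about 34% of trials would exceed 5 points. The average absolute imbalance is about 0.8 × 5.2 ≈ 4 points.

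**4. Effect on the delirium risk difference.** Shift = imbalance × difference in delirium risk between joints. The documents give only one pooled rate, so the gap is assumed.

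| Assumed gap between joints | Shift at 5-point imbalance | Shift at 10-point imbalance |
|---|---|---|
| 2 points | 0.1 | 0.2 |
| 5 points | 0.25 | 0.5 |
| 10 points | 0.5 | 1.0 |

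The target difference is 17 − 7 = 10 points.

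**5. Power gained by adjustment.** Wald test in logistic regression, 166 per arm, 50:50 mix, overall rates held at 17% and 7%. Unadjusted power by this method is 77.7%.

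| Assumed hip-versus-knee odds ratio | Adjusted power | Gain |
|---|---|---|
| 1.5 | 77.9% | 0.2 points |
| 2 | 78.2% | 0.5 points |
| 3 | 78.8% | 1.1 points |

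**6. Room in the models.** Expected events at 166 per arm: 166 × 0.17 + 166 × 0.07 = 28.2 + 11.6 ≈ 40. Named covariates: Model 2 has 5, Model 3 has 5 + 3 = 8, Model 4 has 8 + 10 = 18.

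**7. Continuous outcomes, form of the gain only.** If hip and knee means still differed by d within-joint SDs after baseline adjustment, then with a 50:50 mix surgery type would hold (d²/4) / (1 + d²/4) of the residual variance. That is 0.0625/1.0625 ≈ 6% at d = 0.5 and 0.25/1.25 = 20% at d = 1. These values of d are assumptions; nothing in the documents supports one over another.

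**The case against.** The strongest reply is that nothing here is wrong. Unstratified block randomization is valid, the sample size reproduces, and the choice of prognostic covariates is partly a matter of judgement. The Discussion says the list came from a literature review. On the primary outcome the benefit is close to nil: a shift of 1 point needs both a rare imbalance and a wide gap between joints, and power rises by about 1 point at best under the assumed odds ratios. The secondary outcomes are declared exploratory. All of this stands, and it limits the point to an improvement in precision.

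Several stronger readings are tempting, and the documents do not support them:

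- *The primary odds ratio is biased.* A reader might infer this from the plan's language of confounding. Randomization protects the comparison on average; only chance imbalance in a given trial is in question.
- *The listed covariates, such as smoking or electrolyte status, matter less than surgery type.* The documents give no predictor strengths.
- *All variation between operations stays in the error of the mobility outcomes.* ANCOVA on the baseline measurement may already absorb part of it.
- *Every secondary analysis should carry the term.* Onset, duration, severity, time to discharge criteria and length of stay are analysed by Mann–Whitney with Hodges–Lehmann estimates, and first pump use by log-rank and one-way Cox. None of these takes a covariate as specified.

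What the reply does not remove is that the variable is already collected, fixes a co-intervention and costs almost nothing to include, in a plan that sets out to adjust widely.

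**Conclusion.** The point holds as a low-cost improvement, not as an error. Surgery type should be among the prespecified covariates and is not. The unadjusted comparison and the planned sample size are unaffected.

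For delirium, the consequence is at most about 1 point of risk difference against a target of 10, in the roughly 5% of trials with a 10-point imbalance, plus 0.2 to 1.1 points of power. These figures assume a 50:50 mix, a gap of 2 to 10 points between joints for the shift, and a hip-versus-knee odds ratio of 1.5 to 3 for the power.

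For range of motion, mobility, pain and opioid use the gain may be larger, but the documents do not allow it to be sized. That surgery type is known at allocation is an inference from the eligibility criteria and Table 2.

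**What to change.** 1. List surgery type (THA/TKA) with the baseline variables in 2.7 and 2.14.1.
2. In 2.16, add it to Model 2. Because Models 3 and 4 are built on Model 2, it carries forward and takes Model 4 from 18 to 19 covariates against about 40 expected events. Model 2 is therefore the place to rely on it.
3. Add it as a term in the ANCOVA models (Timed Up and Go, range of motion, Barthel index) and in the GEE models for NRS pain and opioid consumption.
4. Leave the rank-based, log-rank and one-way Cox analyses as they are.
5. Optionally, and only if enrolment has not started, keep separate randomization lists for THA and TKA.

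The analysis change costs one degree of freedom per model, needs no new data and no more patients, and should be fixed before unblinding. It does need an amendment, which under 2.19 goes back to the ethics committee. Separate lists would also mean a second set of envelopes.

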### Double blinding

2.6

This study is double-blinded. According to the allocation scheme, subjects will receive an intravenous infusion of S-ketamine or 0.9% saline during the procedure and a continuous infusion of S-ketamine or 0.9% saline via patient-controlled intravenous analgesia (PCIA) device after surgery. To ensure that the investigators are blinded, the drug administrator ([name], [name]) will prepare two 20 mL syringes (Weigao Group Medical Polymer Products Co., Ltd.) in a separate room filled with S-ketamine at a concentration of 2.0 mg/mL or 0.9% normal saline. The drug administrator will also configure the PCIA device according to the allocation scheme of the subject. The syringes and the PCIA device will look the same. The drug administrator will not be involved in other parts of the trial. Nurses, surgeons, anesthesiologists, outcome assessors, and statistical analysts will be blinded to the subject’s group and intervention throughout the trial. An independent data and safety monitoring board will oversee the practice and will not disclose the allocation group of the subjects until statistical analysis is completed. In an emergency (such as rapid deterioration of the patient’s clinical status), the anesthesiologist may request disclosure of the intervention the subject received or adjust or interrupt the study drug infusion if necessary, which will be documented. Unblinded subjects will be included in the intention-to-treat (ITT) analysis but excluded from the per-protocol (PP) analysis.

### Baseline assessment

2.7

This is a pragmatic clinical trial, so we will identify confounding factors that may impact the primary outcome. The study team ([name], [name]) will visit the patient before surgery and perform a health assessment. The study team will document the subject’s baseline characteristics by consulting the Hospital Information System and via face-to-face interviews. Baseline characteristics that will be collected include the subject’s age, sex, American Society of Anesthesiologists (ASA) physical status classification system (I [healthy], II [mild systemic disease], III [serious systemic disease], and IV [serious systemic disease with persistent life-threatening condition]); BMI, education level (<elementary school, elementary school, and ≥ secondary school), comorbidities (cardiovascular system, central nervous system, respiratory system, urinary system, gastrointestinal system, and hematologic system), electrolyte level (any concentration of potassium, sodium, calcium and magnesium ions above or below the normal range is defined as abnormal), albumin and hemoglobin concentration, smoking status (smoking is defined as continuous or cumulative smoking for more than 6 months or smoking at least 1 cigarette per day and currently smoking. Subjects will otherwise be defined as never smoking), alcohol consumption (alcohol consumption is defined as an average of more than 60 grams of pure alcohol per day for men and more than 40 grams of pure alcohol per day for women), history of falls (falls within the past 6 months), the presence of vision or hearing abnormalities, preoperative pain scores at rest and exercise, and baseline measurements of mental state, attention, thinking, and consciousness levels using the Chinese version of 3D-CAM.

The study team ([name], [name]) will use a Mini-Mental State Examination (MMSE) scale to assess the subjects’ preoperative cognitive function. Dementia will be defined according to the patient’s education level and MMSE (illiteracy <18 points, primary education <20 points, secondary education <23 points, and postsecondary education <24 points). The Patient Health Questionnaire-9 (PHQ-9) evaluates the subject’s mood. A score of 0–4 is normal, while ≥5 is considered diagnostic for depression. The depression screening needs to be combined with the subject’s medical and medication history. The subject’s functional status will be evaluated with the Barthel index (BI), with a score ≥ 40 considered good functional status and a score < 40 considered poor functional status. The frailty status of the subject will be assessed using The FRAIL Scale, with a score of ≥3 considered frailty and a score of <3 considered no frailty. The Pittsburgh Sleep Quality Index will be used to evaluate the sleep quality of the subject over the past 1 month, with a score of 0–7 considered for no sleep problems and a score of 8 for a sleep disorder. The age-adjusted Charlson Comorbidity Index (aCCI) will be used to assess the comorbidities of the subjects.

### Anesthesia and perioperative analgesia

2.8

Subjects received oral celecoxib 200 mg (Pfizer pharmaceutical co., Ltd., Dalian, Liaoning, China) once daily prior to surgery. Subjects will be transferred to the anesthesia induction room on the day of surgery. Peripheral venous access will be obtained and 3-lead ECG, noninvasive blood pressure, and oxygen saturation monitoring will be established. Depending on the type of procedure, each subject will undergo either an ultrasound-guided adductor canal block or an iliac fascial block before anesthesia induction. Twenty minutes after the block, the subject will be transported to the operating room for intraspinal anesthesia. As this is a pragmatic clinical trial, the use of anesthetic drugs and techniques (epidural vs. subarachnoid block) is at the discretion of the anesthesia team that is assigned to each subject. The anesthesiologist can choose the appropriate medication regimen according to their clinical practice. However, the anesthesia team needs to use the study drug according to the guidance of the drug administrator. The team will also be asked to avoid the use of benzodiazepines, dexmedetomidine, S-ketamine, and other NMDA receptor antagonists. During the surgery, the patient’s body temperature will be continuously monitored with a body temperature monitor to maintain their body temperature at 36°C–37°C. Subjects with hypothermia will be treated with a warm air blower. Infusion and transfusion will be performed according to routine procedures, and blood pressure will be maintained within 20% of baseline. Twenty minutes before the end of surgery, the anesthesiologist will administer ondansetron 4 mg (Qilu Pharmaceutical Co., Ltd., Jinan, Shandong, China) to prevent nausea and vomiting. The PCIA device will be activated in the post-anesthesia care unit (PACU). When the subject’s Number Rating Score (NRS) rises above 4 points, they will receive intravenous fentanyl 50 μg (Jiangsu Enhua Pharmaceutical Co., Ltd., Xuzhou, Jiangsu, China) as rescue analgesia. Subjects will be transferred to the surgical ward when they meet the transfer criteria. Subjects will receive flurbiprofen axetil 50 mg (Beijing Taide Pharmaceutical Co., Ltd., Beijing, China) twice daily as basic analgesic therapy. When the subject’s NRS rises ≥4, they will receive an intravenous injection of 50 mg pethidine (Qinghai Pharmaceutical Factory Co., Ltd., Xining, Qinghai, China), which can be repeated every 4–6 h, with a maximum dose of 300 mg per day. Rescue analgesia is adequate when the subject’s NRS is <4 points. In the case of moderate to severe postoperative nausea or vomiting, ondansetron 0.1 mg/kg will be administered intravenously.

### Interventions

2.9

Subjects in the intervention group will receive an intravenous infusion of S-ketamine (Jiangsu Heng Rui Medicine Co., Ltd., Jiangsu, China) following a standard dilution protocol (40 mg S-ketamine with 0.9% normal saline to 20 mL, 2.0 mg/mL). The infusion rate of S-ketamine will be 0.1 mL/kg/h (0.20 mg/kg/h), the infusion mode will be constant speed pumping, and the infusion time will be 1 h. In the control group, subjects will receive 0.9% saline at 0.1 mL/kg/h for 1 h at a constant rate infusion.

All subjects will be transferred to the PACU after surgery. The PCIA device will be connected and started. In the intervention group, the PCIA device will be filled with 1.0 mg/kg S-ketamine, 50 μg sufentanil (Yichang Renfu Pharmaceutical Co., Ltd., Yichang, Hubei, China), 6 mg butorphanol tartrate (Jiangsu Heng Rui Medicine Co., Ltd., Jiangsu, China) and 8 mg ondansetron, diluted to 100 mL with normal saline. In the control group, the PCIA device will not contain S-ketamine. The background dose will be 1 mL/h, the single bolus dose 2 mL, the lockout time 15 min, and the maximum infusion rate 8 mL/h.

The choice of S-ketamine dose and mode of administration was based on published clinical trials and drug manufacturer instructions. S-ketamine is twice as potent in analgesia as ketamine, and the same anesthetic effect can be achieved with a dose of 1/2 ketamine. A subanesthetic dose of S-ketamine (0.25 mg/kg) was often selected by the investigator for the prevention of POD or perioperative neurocognitive dysfunction (Wei et al., 2022; Han et al., 2023; Ma et al., 2023). However, we need to be clear that a dose of 1/2 ketamine may not be equivalent to the dose at which S-ketamine exerts neuroprotective effects, and that relatively high doses of S-ketamine are more prone to adverse events and potential safety concerns (McIntyre et al., 2021). Subjects will receive intraspinal anesthesia rather than general anesthesia in this study, which avoids the influence of other anesthetic drugs on the neuroprotective effects of S-ketamine. In addition, elderly patients with preoperative dementia, depression, and multiple comorbidities will be included, making the dose of S-ketamine received in the intervention group more conservative. Our previous study found that subjects receiving 0.3 mg/kg/h S-ketamine had hallucinations and dreaminess, although this dose was subanesthetic (Zhu et al., 2023). Therefore, we will use a smaller subanesthetic dose of S-ketamine 0.2 mg/kg infused over 1 h in this trial. In antidepressant therapy, the short-term efficacy of intravenous ketamine necessitates repeated dosing in most cases to maintain therapeutic benefit. Therefore, the intervention group will receive an intravenous infusion of 0.010 mg/kg/h for 48 h via the PCIA device after surgery, a dose with fewer psychiatric side effects and maintaining the need for analgesia.

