#### Secondary outcomes

2.11.2

Number of POD episodes. One positive 3D-CAM assessment can be diagnosed as POD. Two consecutive negative 3D-CAM assessments were considered a transition from POD to non-POD status.The onset time and duration of delirium. The onset time of delirium is defined as the time from the subject being transferred back to the surgical ward to the first diagnosis of delirium. The duration of delirium is defined as the time elapsed from the subject’s diagnosis of delirium to 2 negative 3D-CAM assessments. The maximum duration of delirium will be recorded in patients with multiple delirium episodes.Delirium severity score. Patients with established delirium will also be assessed for delirium severity using the CAM-S (Inouye et al., 2014), with daily maximum scores recorded. The CAM-S scale has 4 items with a total score of 7 points. Symptom severity can be classified as absent (0), mild (1), or marked (2). The total score of 0 is normal, 1 is mild delirium, 3–5 is moderate delirium, and 6–7 is severe delirium.Subtypes of delirium. Delirium can be divided into three motoric subtypes according to its clinical manifestations: hyperactive, hypoactive, and mixed. The Richmond Agitation-Sedation Scales (RASS) classify delirium subtypes in patients with established delirium (Ely et al., 2003). Hyperactive delirium is defined as RASS that are consistently positive (+1 to +4); hypoactive delirium is defined as RASS that are consistently neutral or negative (−3 to 0); mixed delirium is defined when some RASS are positive (+1 to +4) and some are neutral or negative (−3 to 0).Pain scores at rest and exercise. Assessments will be performed using the NRS at 8:00–10:00 on postoperative days 1–3, during physical therapy on postoperative days 1–3, and at 16:00–18:00 on postoperative days 1–3. Resting is defined as the subject being in a quiet supine position, and exercise is defined as the subject lifting the affected limb at least 5 times to a height of at least 30 cm.Opioid consumption. Opioid consumption will be assessed on postoperative day 1, postoperative day 2, and overall. Opioid consumption, including PCIA and rescue analgesics, will be converted to a “morphine equivalent dose” for analysis.The time of first analgesia pump compression within 24 h of surgery (defined as the time elapsed from the start of the analgesia pump to its first compression).Post-operative sleep quality: The NRS will be used to assess the subject’s sleep quality on postoperative days 1–3 (on an 11-point scale where 0 = best sleep and 10 = worst sleep).Preoperative baseline and 3 days postoperative Timed Up and Go test. The Timed Up and Go test is the time it takes to get up from a standard-height armchair, walk three meters forward, walk back to the chair, and sit down.The active range of motion of the affected knee or hip at baseline and 3 days after surgery. The active range of motion is defined as the range from neutral (0°) to maximum flexion.BI score at baseline and 3 days after surgery.Time to discharge criteria, which include the subject being able to walk independently from their bed to the bathroom and along a hallway without the aid of a walker.Length of hospital stay. It is defined as the time elapsed from the day of the subject’s procedure to discharge.

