### Data collection

2.14

Data will be collected via face-to-face interviews with subjects and relatives or extracted from the HIS (Table 2).

**Table 2 tab2:** Enrollment schedule, interventions, and assessments.

Outcome measure	Visit 1	Visit 2	Visit3	Visit4	Visit 5	Visit 6	Visit 7	Visit 8
Time	Day of admission	1 day pre-surgery	During operation	6 h post-operative	1 d post-operative	2 d post-operative	3 d post-operative	Hospital discharge
Eligibility screening	X		–	–	–	–	–	–
Informed consent	X		–	–	–	–	–	–
Demographic characteristics	–	X	–	–	–	–	–	–
Baseline measures	–	X	X	–	–	–	–	–
Randomization	X	–	–	–	–	–	–	–
Intervention	Intraoperative S-ketamine will be infused continuously at 0.20 mg/kg/h for 1 h, followed by 0.01 mg/kg/h for 48 h							
Incidence of POD	–	–	–	X	X	X	X	–
Onset time of POD	–	–	–	X	X	X	X	–
Duration of POD	–	–	–	X	X	X	X	X
Severity of POD	–	–	–	X	X	X	X	–
Subtypes of POD	–	–	–	X	X	X	X	–
NRS	–	–	–	–	X	X	X	–
Opioid consumption	–	–	–	–	X	X	–	–
Pump compression	Within 24 h of surgery							
Clinical outcomes	–	X	–	–	–	–	X	–
Length of stay	–	–	–	–	–	–	–	X
Safety outcomes	Throughout the study period until discharge							

POD, postoperative delirium; NRS, number rating score.

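### The stated postoperative S-ketamine regimen of 0.010 mg/kg/h for 48 h is only the pump's background rate; with boluses the same pump can give 0.48 to 1.0 mg/kg

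*Protocol article*

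**What the plan says.** Section 2.9 (Interventions) of the protocol article describes the postoperative treatment twice.

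The first description is the device set-up. In the active arm "the PCIA device will be filled with 1.0 mg/kg S-ketamine, 50 μg sufentanil", with butorphanol and ondansetron in the same mixture, "diluted to 100 mL with normal saline". The control device is the same without S-ketamine. For the settings: "The background dose will be 1 mL/h, the single bolus dose 2 mL, the lockout time 15 min, and the maximum infusion rate 8 mL/h".

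A second description, in the dose rationale, follows later in the section: "the intervention group will receive an intravenous infusion of 0.010 mg/kg/h for 48 h via the PCIA device after surgery". The same sentence defends this as "a dose with fewer psychiatric side effects and maintaining the need for analgesia".

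Table 2 (section 2.14) gives the schedule entry as "Intraoperative S-ketamine will be infused continuously at 0.20 mg/kg/h for 1 h, followed by 0.01 mg/kg/h for 48 h". Section 2.6 (Double blinding) likewise describes the postoperative treatment as a continuous infusion through the patient-controlled device. Neither the rationale nor Table 2 calls 0.010 mg/kg/h a background or minimum rate, and neither mentions boluses.

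Bolus use is expected. Section 2.11.2 lists as a secondary outcome "The time of first analgesia pump compression within 24 h of surgery", and it counts drug from the pump towards opioid consumption.

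**The concern.** The rationale and Table 2 read as a fixed-rate infusion with a known total dose. The set-up describes a demand-driven pump in which S-ketamine shares a reservoir with the opioids, so every press for pain relief also delivers S-ketamine. The article does not say that boluses are free of S-ketamine, that the reservoir is refilled, or what happens if it runs out before 48 h.

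Two things are at stake. The first is the description of the experimental treatment: a report that gives the regimen as 0.010 mg/kg/h for 48 h would be wrong for any patient who used the bolus. The second is the tolerability argument. It is attached to the lowest rate the running pump can give, in a population that section 2.9 says calls for conservative dosing because patients with dementia, depression and multiple comorbidities are included. Exposure in the active arm also depends on demand after surgery, so it varies between patients in a way the stated figure hides.

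**Working it through.** **Inputs** (all from section 2.9): S-ketamine content 1.0 mg/kg; volume 100 mL; background 1 mL/h; bolus 2 mL; lockout 15 min; maximum 8 mL/h; stated regimen 0.010 mg/kg/h for 48 h.

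**Assumptions:** the mixture is uniform, the reservoir is not refilled, the pump runs for up to 48 h, and the 8 mL/h maximum covers background and boluses together.

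**Step 1: reproduce the stated figure.**
- Concentration = 1.0 mg/kg ÷ 100 mL = 0.01 mg/kg per mL.
- Background = 1 mL/h × 0.01 = 0.010 mg/kg/h, which matches exactly.
- Over 48 h: 48 mL, so 48 × 0.01 = 0.48 mg/kg.

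**Step 2: add the bolus.**
- One bolus = 2 mL × 0.01 = 0.02 mg/kg, equal to 2 h of background.
- Rate = 0.01 × (1 + 2 × boluses per hour), limited to 0.01 × 8 = 0.08 mg/kg/h.
- Time to empty = 100 ÷ flow in mL/h.
- Dose over 48 h = rate × 48, limited to the 1.0 mg/kg in the reservoir.

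| Bolus use | Flow (mL/h) | Rate (mg/kg/h) | Reservoir empty at | Dose over 48 h (mg/kg) |
|---|---|---|---|---|
| None | 1 | 0.010 | not within 48 h | 0.48 |
| One every 4 h | 1.5 | 0.015 | not within 48 h | 0.72 |
| One every 2 h | 2 | 0.020 | not within 48 h | 0.96 |
| One per hour | 3 | 0.030 | 33.3 h | 1.0 |
| Two per hour | 5 | 0.050 | 20 h | 1.0 |
| At the maximum | 8 | 0.080 | 12.5 h | 1.0 |

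**Step 3: when does the pump run out early?**
- Volume left for boluses over 48 h = 100 − 48 = 52 mL, and 52 ÷ 2 = 26 boluses.
- 48 ÷ 26 = 1.85 h, so more than about one bolus every 1.85 h on average ends the infusion before 48 h.

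**Step 4: size against the stated regimen.**
- Cumulative: 1.0 ÷ 0.48 = 2.08 times at most.
- With the intraoperative 0.20 mg/kg included: (0.20 + 1.0) ÷ (0.20 + 0.48) = 1.20 ÷ 0.68 = 1.76 times at most.
- Hourly ceiling: 0.08 ÷ 0.010 = 8 times, for no longer than 12.5 h.

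**If the maximum applies to boluses only:** the 15 min lockout allows 4 × 2 = 8 mL/h, plus 1 mL/h background = 9 mL/h. That is 0.09 mg/kg/h, with the reservoir empty at 100 ÷ 9 = 11.1 h. The cumulative limit of 1.0 mg/kg does not change.

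**The case against.** The strongest reply is that nothing has been miscalculated. The figure of 0.010 mg/kg/h is exactly the continuous component, sections 2.6 and 2.14 use the language of continuous infusion, and the full settings are disclosed in section 2.9. Staff preparing the pump would follow those settings and meet no rival instruction. On this view all that is missing is the word background in two places. The first part stands: this is an inconsistency of description, not an arithmetic error. But the missing word changes the meaning. The rationale and Table 2 state a rate and a duration for what the group receives, and the settings make that true only for a patient who never presses the button in 48 h.

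Four stronger readings are tempting, and the document does not support them.

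- *Patients will receive eight times the stated dose.* Eightfold is an hourly ceiling that needs near-maximal demand. The total cannot exceed 2.08 times. Section 2.8 also provides a nerve block, celecoxib, flurbiprofen and rescue opioids, which may hold demand down. No bolus frequency is given, so typical exposure cannot be stated.
- *The permitted exposure goes beyond what the protocol discusses.* Even 0.08 mg/kg/h is below the intraoperative 0.20 mg/kg/h and below the 0.3 mg/kg/h at which section 2.9 reports hallucinations in the group's previous study. The rationale omits the boluses; that does not show the exposure is unsafe.
- *The primary comparison is invalid.* The primary analysis in section 2.16 is by intention to treat. It compares randomised pumps as configured, and demand-dependent dosing is part of that assigned strategy.
- *Heavy users would be removed from the per-protocol set.* Section 2.16 refers only to incomplete adherence to trial medication. Nothing says that a patient who received the whole reservoir counts as non-adherent, and the working definition may sit in an analysis plan that is not shown.

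**Conclusion.** The point holds as an internal inconsistency in the dose description. Section 2.9's rationale and Table 2 present the minimum postoperative rate as the regimen. Under the pump settings in the same section, the postoperative dose can range from 0.48 to 1.0 mg/kg, and more than 26 boluses end the infusion before 48 h. This rests on boluses coming from the S-ketamine mixture, which the set-up implies and nothing contradicts, and on there being no refill, on which the article is silent. Where patients will fall in the range is unknown.

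The consequence is one of interpretation. The randomised comparison is sound, but the treatment it evaluates is a demand-driven pump. The stated dose and its tolerability argument describe only patients who take no bolus.

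**What to change.** Reconcile the treatment description in section 2.6, the pump settings and dose rationale in section 2.9, and the intervention row of Table 2, so that all describe the same regimen. Which regimen that is remains for the investigators to settle. If the pump settings stand as written, the text should identify 0.010 mg/kg/h as the background rate, give the range that boluses allow, and say what happens if the reservoir empties before 48 h.

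Derive delivered postoperative S-ketamine for each active-arm patient as pump volume (mL) × 0.01 mg/kg per mL, and report it by day and overall. Section 2.11.2 already needs pump use on days 1 and 2 to calculate opioid consumption, so no new data are required. The trial's conclusion can then refer to the dose actually given.

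Cost: one protocol clarification and one derived variable.
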